### Blinding

OPTION-DM is a double-blind study and blinding of medication will be maintained with over-encapsulated drugs and matching placebos. The treating physician will be aware of the dose level but not the treatment itself. Due to the complex dosing schedule, the pharmacist at each study centre will be unblinded and a member of staff at Sheffield CTRU responsible for site monitoring will also be unblinded.

Emergency unblinding can be performed where the knowledge of the treatment allocation would change the participant’s clinical management or to facilitate safety reporting to the regulatory authority and Research Ethics Committee.

### Adherence

Participants will be provided with detailed guidance regarding how to take their study medication. This will be reinforced with written instructions and participants will be directed to complete a daily medication diary to record which doses they have taken.

Participants will be asked to return all bottles of study medication, including empty bottles and any unused medication. These will be reviewed and the remaining capsules counted to monitor adherence to study treatment. The study nurse will provide further guidance to participants if there is concern about adherence levels.

### Concomitant medications

Participants will maintain their current schedule of treatment throughout the duration of the study. Changes to concomitant medications will be documented at each study visit. Participants may take paracetamol 1 g (up to a maximum dose of four times a day (QDS)) for pain throughout the study period.

The following concomitant medications are prohibited during the study period: opioid analgesia, capsaicin cream/high-dose capsaicin patches, lidocaine patches, anti-inflammatory medications (e.g. diclofenac, colecoxib), other antiepileptic medications (e.g. carbamazepine), other antidepressant medications (e.g. SSRIs, MAOIs), other neuropathic pain medications (e.g. venlafaxine, intravenously administered (IV) lignocaine, etc.), use of any medications that could lead to potentially serious interactions with study medications.

### Blood sample collection

Blood samples will be stored for future research which may include genetic analysis. Samples will be obtained at the same time as other study blood samples from participants who have given additional (optional) consent. The blood will be frozen and stored locally before being shipped to a central laboratory.

### Study procedures

The study assessment schedule (SPIRIT Figure; Fig. 3) below details the assessments required during the course of one treatment pathway. All participants will complete three treatment pathways and this schedule will be repeated from week 0 to week 16 until all three pathways are complete. Week 17 will only be relevant at the end of the final pathway.

**Fig. 3 Fig3:**
[figure not shown]
Study assessment schedule (Standard Protocol Items: Recommendations for Interventional Trials (SPIRIT) Figure). ^a^This visit is only required prior to randomisation, i.e. before starting the first treatment pathway. ^b^ Between scheduled study visits, the research nurse will contact the participant by telephone each week (a minimum of once per week). The nurse will confirm compliance with medication and remind the participant to complete study diaries/questionnaires. ^c^ Visits must normally be within ± 2 days of the scheduled visit date. Scheduled visit dates relate to the date of the previous visit. Where this is impossible, e.g. due to bank holidays or patient availability. ^d^ Week-8 visit only required for participants on combination treatment. ^e^ At the week-16 visit, participants will be given instructions to tape-off the current study treatment. Visits from week 0 to week 16 will be repeated until all 3 pathways have been completed. ^f^ Week 17 is only applicable following the final pathway. ^g^ FBC, urea and electrolytes, liver function tests, glycosylated haemoglobin A1c and serum creatinine. ^h^ hole blood sample to be collected and stored for future research. The sample can be obtained at the same time as any scheduled blood test for the study. Please refer to the *OPTION-DM Sample Collection Manual* for details. ^i^ Height (at week − 2 only), weight, heart rate and blood pressure (lying and standing). ^j^ To be completed by participants daily during the study, starting during the washout period. Pain scores may also be collected via daily text messages where participants have given additional consent for this. ^k^ Only required at week 0 of pathway 1, i.e. randomisation visit. ^l.^Not required at week 0 of pathway 1, i.e. randomisation visit

### Primary outcome

The primary outcome is the difference between 7-day average 24-h pain (evaluated at patient level) on an 11-point NRS scale (0 = no pain and 10 = worst pain imaginable) measured during the final follow-up week of the treatment cycle (week 16) among pathways. The NRS 24-h average pain is now considered the ‘gold standard’ for the assessment of neuropathic pain and has been employed in almost all well-designed neuropathic pain studies over the past 10 years [15, 20, 21].

### Secondary outcomes

#### Efficacy

Difference between 7-day average 24-h pain (evaluated at patient level) on an 11-point NRS scale at week 6 among monotherapiesDifference between RAND short form 36 (RAND SF-36) physical mean scores (evaluated at patient level) at week 16 among pathways [22]Difference between RAND SF-36 physical mean scores (evaluated at patient level) at week 6 among pathways [22]Difference between RAND SF-36 mental mean scores (evaluated at patient level) at week 16 among pathways [22]Difference between RAND SF-36 mental mean scores (evaluated at patient level) at week 6 among pathways [22]Difference between Hospital Anxiety and Depression Scale (HADS) mean anxiety scores (evaluated at patient level) at week 6 among pathways [23].Difference between Hospital Anxiety and Depression Scale (HADS) mean anxiety scores (evaluated at patient level) at week 16 among pathways [23]Difference between Hospital Anxiety and Depression Scale (HADS) mean depression scores (evaluated at patient level) at week 6 among pathways [23]Difference between Hospital Anxiety and Depression Scale (HADS) mean depression scores (evaluated at patient level) at week 16 among pathways [23]Difference in proportion of patients having treatment success (30%) at week 16 among pathways. Treatment success is defined as a reduction in 30% value of 7-day average NRS score at follow-up compared to baselineDifference in proportion of patients having treatment success (50%) at week 16 among pathways. Treatment success is defined as a reduction in 50% value of 7-day average NRS score at follow-up compared to baseline

Difference in Brief Pain Inventory – modified short form (BPI-MSF) measure of pain interference with function total score (evaluated at patient level) at week 6 among pathways [24]12.Difference in BPI-MSF measure of pain interference with function total score (evaluated at patient level) at week 16 among pathways [24]13.Difference in Insomnia Severity Index (evaluated at patient level) total score at week 6 among pathways [25]14.Difference in Insomnia Severity Index (evaluated at patient level) total score at week 16 among pathways [25]15.Difference in Patient Global Impression of Change (evaluated at patient level) at week 16 among pathways [26]16.Difference in proportion of care pathway preferred by participants at week 50

#### Cost-effectiveness

17.EuroQoL-5D-5 L: the EQ-5D is a routinely used generic HRQL instrument. It is the preferred instrument for assessing HRQL by NICE, and the newer five-level (EQ-5D-5 L) instrument offers increased sensitivity as opposed to the original three-level version [27]18.A modified version of the Client Service Receipt Inventory (CSRI): the CSRI is a routinely used instrument to capture health resource use and personal expenses. Unnecessary questions will be removed to reduce participant burden [28]

#### Safety

20.Frequency and proportion of patients reporting at least one Adverse Event for each of the pathway. Additionally, the relationship to intervention (Definite, Probable, Possible, Unlikely, Unrelated, Not assessable) will be reported (frequency and proportion)21.Frequency and proportion of Adverse Events for each of the pathways22.Listing of Adverse Events for each of the pathways23.Frequency and proportion of patients reporting at least one Serious Adverse Event for each of the pathways. Additionally, these characteristics will be summarised (frequency and proportion): intensity (Mild, Moderate, Severe), relationship (Definite, Probable, Possible, Unlikely, Unrelated, Not assessable), is SUSAR, is Death24.Frequencies of Serious Adverse Events for each of the pathways25.Listing of Serious Adverse Events for each of the pathways

#### Subgroup

Neuropathic Pain Symptom Inventory (NPSI) questionnaire for subgroup analysis relating pain phenotype to treatment response [29]. There is emerging evidence that treatment response may be determined by a patient’s pain phenotype [30–32]. In particular, these outcomes will be evaluated:26.Difference between ‘Burning (superficial) spontaneous pain’ NPSI mean subscores – (evaluated at patient level) at week 6 among pathways27.Difference between ‘Burning (superficial) spontaneous pain’ NPSI mean subscores – (evaluated at patient level) at week 16 among pathways28.Difference between ‘Pressing (deep) spontaneous pain’ NPSI mean subscores – (evaluated at patient level) at week 6 among pathways29.Difference between ‘Pressing (deep) spontaneous pain’ NPSI mean subscores – (evaluated at patient level) at week 16 among pathways30.Difference between ‘Paroxysmal pain’ NPSI mean subscores – (evaluated at patient level) at week 6 among pathways31.Difference between ‘Paroxysmal pain’ NPSI mean subscores – (evaluated at patient level) at week 16 among pathways32.Difference between ‘Evoked pain’ NPSI mean subscores – (evaluated at patient level) at week 6 among pathways33.Difference between ‘Evoked pain’ NPSI mean subscores – (evaluated at patient level) at week 16 among pathways34.Difference between ‘Paresthesia/dysaesthesia’ NPSI mean subscores – (evaluated at patient level) at week 6 among pathways35.Difference between ‘Paresthesia/dysaesthesia’ NPSI mean subscores – (evaluated at patient level) at week 16 among pathways36.Difference between NPSI mean total scores – (evaluated at patient level) at week 6 among pathways37.Difference between NPSI mean total scores – (evaluated at patient level) at week 16 among pathways

### Patient-perceived tolerability

38.Difference between tolerability (evaluated at patient level) on an 11-point NRS scale at week 16 among pathways-.39.Difference between tolerability (evaluated at patient level) on an 11-point NRS scale at week 6 among monotherapies

### Sample size

A 1-point change in an individual on the NRS scale is considered a minimum clinically important difference [33]. Hence, the proportion of patients improving by at least 1 point would seem a suitable outcome. However, we have based the sample size calculation on a continuous outcome, the mean change between groups in order to maintain power [34]. We have chosen a mean change at the population level of 0.5 points between groups based on the effect size previously reported for comparison of two active interventions for neuropathic pain in a crossover study [35]. Based on Normal Distribution Theory we estimate that a 0.5-point shift in population means will lead to an additional 8% of individual patients achieving a 1-point improvement [36]. We have also used a conservative, Bonferroni-corrected significance of 1.67% in order to retain an overall 5% false-positive probability for finding a significant pairwise comparison. Using a within-patient SD of 1.65 [35], an alpha of 0.0167 and 90% power, we require 294 evaluable patients [37]. Assuming a 25% dropout rate 392 patients will be randomised to ensure that 294 patients are expected to complete the study.

### Withdrawals

An individual participant may stop treatment early for any of the following reasons:Unacceptable toxicityWithdrawal of consent for treatment by the participantInter-current illness which prevents further treatmentAny alteration in the participant’s condition which justifies the discontinuation of treatment in the investigator’s opinionPregnancy

Participants will be followed up as per the trial schedule until the end of the current treatment pathway, provided they are willing. A discussion will also take place to clarify whether the participant is discontinuing all study treatment or whether they wish to return for the next treatment pathway.

When a participant stops treatment in the OPTION-DM study, they will return to their usual care provider for treatment outwith the study. At the end of the trial, when the final analysis has been completed, the CTRU will provide participating sites with the unblinded treatment allocations for each of their participants. The site staff will be responsible for contacting each of the participants to notify them of the treatment allocations. It will then be a clinical decision between the participant and their usual care provider as to which treatment they receive.

### Data collection and management

Participant confidentiality will be respected at all times and the principles of the UK Data Protection Act (DPA) will be followed. The study will use the CTRU’s in-house data management system (Prospect) for the capture and storage of study-specific participant data. Access to Prospect is controlled by usernames and encrypted passwords, and a comprehensive privilege management feature will be used to ensure that users have access to only the minimum amount of data required to complete their tasks. A member of staff at each site will enter data from source documents into the study-specific Prospect database when available. After data have been entered, electronic validation rules are applied to the database on a regular basis; discrepancies are tracked and resolved through the Prospect database. Questionnaires are self-completed by participants and entered onto the study database by the research nurse. Data will be stored and managed in accordance with CTRU Standard Operating Procedures (SOPs).

### Statistical analysis

The statistical analysis will be reported according to Consolidated Standards of Reporting Trials (CONSORT) guidelines [38] and using an intention-to-treat approach as the primary analysis. As three pairwise comparisons will be performed, all statistical tests will be two-tailed at a 1.67% significance level. The primary outcome and other continuous outcomes will be analysed using a random-effects model with participant, treatment, sequence and period entered into the model. Participant will be entered as a random term. Contrasts will be used to evaluate the difference in means. Three 98.33% confidence intervals for the difference on treatment effect will be reported as well as the associated *P* value.

In case of missing data, the missing data mechanism will be explored and multiple imputation may be applied as a sensitivity analysis as appropriate. Other sensitivity analyses will be performed in order to evaluate the robustness of the primary analyses [39].

A logistic regression will be undertaken to analyse binary outcomes using a model similar to that for the continuous outcomes. Differences between treatment groups will be reported as odds ratios with associated 98.33% confidence intervals and *P* values. Full details of the statistical analyses will be specified in a detailed Statistical Analysis Plan.

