### Study objectives

To evaluate if at least one of the three pathways is superior to the other pathways in terms of pain symptoms, quality of life and cost-effectivenessTo evaluate if at least one monotherapy is superior to a different monotherapy in improving pain symptomsTo describe Adverse Event and Serious Adverse Event data for the different treatment pathways for DPNPTo conduct an exploratory analysis to investigate whether there are patient phenotypes that predict response to treatment

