## Methods/design

### Study design

OPTION-DM is a multicentre, double-blind, centre-stratified, multi-period crossover study with equal allocation to sequences (1:1:1:1:1:1) of treatment pathways. Three hundred and ninety-two participants will be recruited from secondary care DPNP centres in the UK. A list of participating centres can be found at the end of this paper. Recruitment is expected to take place over 12 months beginning in October 2017. Follow-up will continue for another 12 months.

The study contains an internal pilot with stop-go criteria to assess its feasibility. The recruitment and retention will be reviewed in relation to targets agreed with the funder after 6 months of recruitment. If met, an assessment of attrition to the trial is scheduled after 12 months of recruitment.

The study protocol was written in accordance with the Standard Protocol Items: Recommendations for Interventional Trials (SPIRIT) guidelines (see Additional file 1: SPIRIT Checklist).

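### Shaffer's step-down would raise the chance of showing one pathway better than both others at the same 5% familywise error; the flat 1.67% rule is valid but leaves that power unused

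*Protocol article*

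**What the plan says.** Under Statistical analysis, the protocol article sets a single level: "As three pairwise comparisons will be performed, all statistical tests will be two-tailed at a 1.67% significance level". It pairs this with three 98.33% confidence intervals for the primary outcome and applies the same interval level to the odds ratios for binary outcomes. No global, stepwise or closed procedure is mentioned.

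Under Sample size, the reason given is a "conservative, Bonferroni-corrected significance of 1.67% in order to retain an overall 5% false-positive probability for finding a significant pairwise comparison". The planning difference is stated as "We have chosen a mean change at the population level of 0.5 points between groups". With a within-patient SD of 1.65, alpha of 0.0167 and 90% power, this gives 294 evaluable patients, and 392 randomised after 25% dropout.

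Under Study objectives, the first aim is "To evaluate if at least one of the three pathways is superior to the other pathways". The article gives no power for a pathway beating both others.

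**The concern.** Bonferroni treats the three pairwise hypotheses as if any combination of them could be true. With three means that is not so: if any two pairs are equal, all three are. Once one pair truly differs, at most one null hypothesis remains that could be falsely rejected, so holding the remaining tests at 1.67% protects against an error that cannot occur.

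This matters because of the question the trial asks. To name one pathway as better than the other two, two comparisons must both succeed. The stated 90% applies to one comparison. Power for the pair of wins is lower, and the flat rule lowers it further than the 5% familywise target demands. Because the rule covers all statistical tests, the secondary outcomes are affected in the same way.

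**Working it through.** **Inputs (Sample size section).** Difference d = 0.5; within-patient SD s = 1.65; two-sided alpha 0.0167; power 90%; 294 evaluable; dropout 25%. Every participant is to receive all three pathways, so two contrasts that share a pathway correlate at 0.5.

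**The plan's own figures.**
- n = 2 × [s(z₁₋α/₂ + z₀.₉₀)/d]² = 2 × [1.65 × (2.393 + 1.282)/0.5]² = 294.1. This agrees with 294 (295 if rounded up).
- 294/0.75 = 392, exactly as stated.
- The standard error of a contrast is 1.65 × √(2/294) = 0.136, and 0.5/0.136 gives a noncentrality of 3.674.
- Power for one pair at 1.67% (critical value 2.394) is Φ(3.674 − 2.394) = 90.0%.

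**Power to beat both others, flat rule.** Take one pathway 0.5 better than two equal ones. Both standardised contrasts must exceed 2.394. The bivariate normal probability with correlation 0.5 is 83.2%. The flat rule would need about 344 evaluable patients to reach 90% on this target.

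**Why a step-down is valid.** Shaffer's rule tests the smallest p-value at 0.05/3. If all three nulls are true, a false claim needs that first step to succeed, which Bonferroni holds to at most 5%. If exactly one null is true, it is tested at no more than 5%. Exactly two true nulls is impossible. Familywise error is therefore at most 5% in every case. Every pair that Bonferroni rejects has p ≤ 1.67%, so the first step passes and that pair is rejected here too.

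**Comparison at 294 patients** (simulation, normal contrasts, known variance):

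| | Flat 1.67% | Shaffer | Global 5%, then pairs at 5% |
|---|---|---|---|
| Means 0, 0, 0.5: best pathway beats both | 83.2% | 91.6% | 92.2% |
| Same: a given 0.5-point pair | 90.0% | 94.2% | 94.8% |
| Same: at least one of the two true differences | 96.7% | 96.7% | 97.4% |
| Means 0, 0.25, 0.5: end pathway beats both | 28% | 44% | 44–45% |
| Same: the 0.5-point pair | 90% | 91% | 91–92% |
| Familywise error, all equal | 4.4% | 4.4% | 5.0% |
| Familywise error, two equal | 1.7% | 5.0% | 5.0% |

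Using t and F tests with estimated variance changes little: power to beat both in the first scenario is 83.0%, 91.5% and 92.1%. Holm's procedure, which ignores the logical link, reaches 87.0%.

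**Agreement with the 98.33% intervals.** Under the flat rule each test matches its interval. Under Shaffer, some pair is significant while its 98.33% interval includes zero in about 11% of trials with means 0, 0, 0.5 and about 29% with means 0, 0.25, 0.5.

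**The case against.** The strongest reply is that nothing here is wrong. The sample size reproduces, 90% is correct for one comparison, error is controlled within each outcome, design and analysis use the same alpha, and the article itself calls the correction conservative. Single-step tests that always match their intervals are a legitimate choice in a trial meant to inform guidance. All of this stands, and it is why the point is an efficiency gain and not a defect.

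The size of the gain also depends on the target. The Sample size section speaks of finding a significant pairwise comparison. For finding any pair Shaffer adds nothing, because its first step is the Bonferroni test. For the 0.5-point pair in the graded scenario the gain is about one percentage point. The large gain needs the first objective to mean beating both others. That is a natural reading, but the article states no such win criterion.

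Three stronger readings are tempting and are not supported:
- A reader might infer that the trial is underpowered or its power misstated. It is not: 90% per pair is what was planned and what the inputs give.
- A reader might infer that a global 5% test followed by 5% pairwise tests dominates the current rule. It does not. If the third pathway lies midway, the 2-df global statistic equals z² for the outer pair, and its 5% critical value of 5.99 requires |z| > 2.448, whereas Bonferroni needs only 2.394. The loss is rare (about 0.06% of trials with means 0, 0, 0.5 and 0.26% with 0, 0.25, 0.5), but only Shaffer never loses a Bonferroni rejection.
- A reader might infer that the change is free. The disagreement between tests and intervals is its price.

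That full statistical detail is left to a separate analysis plan mitigates only in part, because the 1.67% level for all tests is fixed in this article.

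**Conclusion.** The plan is valid and a cheap improvement is available. With the same 294 evaluable patients and the same 5% familywise error, Shaffer's step-down raises power to show one pathway better than both others by about 8 points (83% to 92%, from 83.2% and 91.6%) when it is 0.5 better than two equal pathways. With means 0, 0.25 and 0.5 the gain is about 16 points (28% to 44%), although power for that goal remains low under either rule. Power to detect any pair is unchanged.

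These figures rest on the protocol's difference and SD, on 294 patients contributing all three periods, on equal variances with no carry-over, and on reading the first objective as requiring two wins.

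**What to change.** **Statistical analysis section.** Replace the flat level with Shaffer's step-down for the three pathway contrasts of the primary outcome, and do the same within each secondary outcome now tested at 1.67%. The smallest p-value is tested at 1.67% and, if significant, the other two at 5%. Report adjusted p-values: with ordered values p₁ ≤ p₂ ≤ p₃, these are 3p₁, max(3p₁, p₂) and max(3p₁, p₃), capped at 1 and compared with 5%. Keep the 98.33% intervals for estimation, and state that the adjusted p-value governs the claim where the two disagree.

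**Sample size section.** State that 90% is the power for one pair, and give the power for beating both others with its assumed means.

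A global 5% test followed by 5% pairwise tests would be a valid alternative with slightly higher power. If it is chosen, the text should acknowledge that it can occasionally miss a pair that Bonferroni would find.

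**Cost.** One paragraph, written before unblinding, with no additional patients, visits or data. A team that prefers every test to match its interval may keep the flat rule, but should then say so and report the 83%.

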### Eligibility criteria

#### Inclusion criteria

Participant aged ≥ 18 yearsNeuropathic pain affecting both feet and / or hands for at least 3 months or taking pain medication for neuropathic pain for at least 3 monthsBilateral distal symmetrical neuropathic pain confirmed by the Douleur Neuropathique 4 (DN4) questionnaire at the screening visit [18]Bilateral distal symmetrical polyneuropathy confirmed by a modified Toronto Clinical Neuropathy Score (mTCNS) > 5 at the screening visit [19]Stable glycaemic control (HbA1c < 108 mmol/mol)Participants will have a mean total pain intensity of at least 4 on an 11-point numeric rating scale (NRS; with 0 being ‘no pain’ and 10 ‘worst pain imaginable’) during 1 week off pain medications (baseline period)Willing and able to comply with all the study requirements and be available for the duration of the study. This will be a 1-year study in which all participants will undergo all treatment pathways regardless of treatment response and this point will be made clearWilling to discontinue current neuropathic-pain-relieving medicationsInformed consent form for study participation signed by participant

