### Washout and baseline period

After providing consent, participants will be instructed on how to washout neuropathic pain medication. The dose will be tapered for 3 days with complete washout for 1–4 days at the investigator's discretion. If the participant is on combination therapy then all drugs will be tapered at once. For participants taking 50-100-mg morphine equivalent the dose will be tapered over a period of up to 2 weeks.

Following the initial washout period, participants will enter the baseline period for 1 week. No neuropathic pain medication is permitted during this week with the exception of paracetamol. From the daily pain scores collected during the baseline period, a mean for the week will be determined and used in subsequent analysis.

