#### Randomisation

Participants will be centrally randomised in the study by the study team at site using the Clinical Trials Research Unit (CTRU) online randomisation system. All participants will receive all three treatment pathways (Table 1). Randomisation will determine the order in which they receive the treatment pathways. Participants will be assigned to one of the six sequences based on a predetermined randomisation schedule stratified by study site using permuted blocks.

**Table 1 Tab1:** Treatment sequences (A = amitriptyline, P = pregabalin, D = duloxetine)

	Treatment pathway 1	Treatment pathway 2	Treatment pathway 3
Sequence 1	A-P	D-P	P-A
Sequence 2	A-P	P-A	D-P
Sequence 3	D-P	A-P	P-A
Sequence 4	D-P	P-A	A-P
Sequence 5	P-A	A-P	D-P
Sequence 6	P-A	D-P	A-P

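### The primary model leaves out the pre-randomisation pain mean; adding it is a free safeguard against dropout whose link to baseline pain differs by pathway

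*Protocol article*

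**What the plan says.** The Statistical analysis section names the terms of the model for the primary and other continuous outcomes: "participant, treatment, sequence and period entered into the model". It adds: "Participant will be entered as a random term". Binary outcomes get a logistic model of similar form. Neither baseline pain nor study site is listed.

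The Washout and baseline period section says of the daily scores from the drug-free week that "a mean for the week will be determined and used in subsequent analysis", without naming the analysis. The inclusion criteria require that weekly mean to be at least 4, so every eligible participant has the value. Under Secondary outcomes, the 30% and 50% treatment-success outcomes are defined against baseline.

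Participants are allocated to the six sequences by a "predetermined randomisation schedule stratified by study site using permuted blocks". The Sample size section assumes 25% dropout. Under Withdrawals, a participant who stops treatment is followed to the end of the current pathway if willing, and staff will "clarify whether the participant is discontinuing all study treatment or whether they wish to return for the next treatment pathway".

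**The concern.** A crossover analysis normally gains little from a baseline covariate, because each participant is his or her own control. That holds fully only when each participant supplies all the pathways. Once some week-16 scores are missing, a model with a random participant term also compares different participants across pathways. Those comparisons are fair only if the participants observed on each pathway have similar underlying pain, given what the model conditions on.

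Suppose participants with worse baseline pain are lost more often on one pathway than on the others. The participants observed on that pathway then have milder pain, and the pathway looks better than it is. Baseline pain would explain the pattern completely, but the listed model does not contain it. The quantity at stake is the primary contrast, which the trial is sized to detect at 0.5 points.

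**Working it through.** **Inputs from the protocol article.** Within-patient SD 1.65, target difference 0.5, two-sided alpha 0.0167, power 90%, dropout 25% (Sample size; Statistical analysis). Three pathways, six sequences, equal allocation (Randomisation).

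**Inputs not in the document, assumed.** Between-patient SD 1.0 to 2.2; correlation of baseline pain with the participant effect 0.5 to 0.8; log-odds slope of dropout on baseline 0.5 to 1.0 per SD; where site is modelled, 20 sites with SD 0.5.

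**Step 1: the plan's own figure.** n = 2 × [SD × (z for alpha/2 + z for power) / difference]² = 2 × [1.65 × (2.393 + 1.282) / 0.5]² ≈ 294. Then 294 / 0.75 = 392. Both stated numbers reproduce. They rest on the within-patient SD, so a baseline covariate does not change them.

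**Step 2: complete data.** Write a participant's score on a pathway as sequence + period + treatment + u + e, where u is the participant effect. Baseline pain and site are constant within a participant and act only through u, which cancels from any within-participant difference. The standard error of a contrast is 1.65 × √(2/392) = 0.118. The simulated standard error is also 0.118, with or without baseline and site.

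**Step 3: incomplete data.** Participants with a missing pathway contribute some between-participant information, in which u does not cancel. If dropout depends on baseline in the same way in every pathway, the mean of u among those observed shifts equally across pathways (period terms absorb any drift over time), and the contrast is unaffected. If the dependence differs by pathway, the means of u differ and part of that difference enters the contrast.

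**Step 4: size.** The design was simulated with the model as listed and again with baseline added. Bias is in NRS points.

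| Missing-data pattern | Participants with a missing pathway | Bias, model as listed | Bias, baseline added |
|---|---|---|---|
| Same baseline relation in all pathways, no return | about 32% | at most 0.008 (Monte Carlo SE 0.003-0.004) | the same |
| Relation in one pathway only, no return | 25-30% | about 0.01-0.03 | at most 0.007, simulation noise |
| Relation of opposite sign in two pathways, no return | about 33% | 0.03-0.06 on the worse contrast | at most 0.006 |
| Relation in one pathway only, return allowed | 28-30% | about 0.02-0.05 | at most 0.006 |

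A further set of pathway-specific scenarios, with roughly 25-30% of participants missing a pathway, gave 0.005-0.035 without return and 0.01-0.06 with return. The overall range is therefore about 0.005-0.06.

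**Step 5: scale.** 0.005 / 0.5 = 1% and 0.06 / 0.5 = 12% of the target difference. 0.06 / 0.13 = 0.46 of a standard error. With opposite signs in two pathways, the rejection rate under no true difference was 0.014-0.032 against a nominal 0.0167, from 1,500 replicates (Monte Carlo SE √(0.0167 × 0.9833 / 1500) = 0.003).

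**Step 6: precision and site.** Adding baseline trims the standard error by about 0.3%. Adding site as well had no material effect in any scenario.

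The figures apply to the continuous primary outcome. The logistic models were not simulated.

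**The case against.** Much of the case against stands, and it rules out four stronger readings.

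- **A contradiction with the baseline section.** A reader might take the promise to use the baseline mean as a promise to adjust for it in the primary model. The sentence does not say that, and the 30% and 50% success outcomes already give it a use.
- **Any baseline-related dropout biases the contrasts.** It does not. The relation has to differ between pathways, and nothing in the document shows that it does. It is plausible: worse pain leads to more dose escalation and more combination therapy, and the drugs may differ in tolerability. It remains an assumption.
- **A bias of 0.05-0.10 points.** Figures of that size appear with about 25-27% loss on each pathway and return allowed, well beyond 25% dropout overall. The Discussion section on 16-week pathways also expects flexible dosing and frequent contact to reduce dropout.
- **Leaving out site is a fault.** Site is constant within a participant and the random participant term absorbs it. Adding it is a matter of convention.

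Two further points limit the size. Stopping treatment is not the same as a missing week-16 score, since follow-up continues for those willing. Scores from a participant's other pathways are in the likelihood and carry some information on severity.

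The last objection is that covariates may be settled in the SAP, which is not shown. That is possible. But the article does not leave the model terms open: it lists them, and baseline is not among them. The planned exploration of missing data and the possible multiple imputation are sensitivity work and leave the primary estimate on the listed model.

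**Conclusion.** The point holds as a small, free improvement in robustness to missing data. The listed primary model is valid with complete data and under dropout related to baseline equally in all pathways. It is open to a bias of about 0.005-0.06 points if the baseline-dropout relation differs by pathway and roughly 25-30% of participants miss a pathway. The size depends on the assumed between-patient SD, correlation and dropout slope, none of which the document gives. At that size the bias alone would rarely change a conclusion, and the planned 294 evaluable and 392 randomised are unaffected.

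**What to change.** In the Statistical analysis section, and in the SAP to match, add the pre-randomisation 7-day mean NRS score as a fixed covariate in the primary random-effects model and in the models for the other pain outcomes, including the logistic models for 30% and 50% success. The same sentence would make clear which analyses use the baseline mean. Study site may be added to match the stratified randomisation, with no material effect expected.

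The cost is one sentence and one degree of freedom for baseline. The value is already collected at eligibility, so no new data, visits or participants are needed.
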